### Approaching patients post-operatively

Where possible, the patient will be approached at a clinically suitable time approximately 48 h (± 4 h) following their operation. However, in order to facilitate patient recruitment and because successful collection of a sufficient number of pre-operative CSF samples is the priority for this study, sites are encouraged to screen and recruit patients from Monday-Friday. This is on the understanding that should a patient be consented on a Thursday/Friday, it may not be possible to complete the 48-h follow-up due to insufficient Research Nurse cover during weekends.

During the 48-h follow-up point, we will aim to collect the post-operative blood sample and Mini-Mental State Examination - 2nd Edition, Short-Form version (MMSE~ 2: SV) data. As appropriate, the research nurse will remind the patient of the study, reassess capacity (as required) and complete pre-consented study related procedures. In English sites, for patients who previously provided informed consent on their own behalf but are as assessed as having since lost capacity at this follow-up point, we will seek a personal or nominated consultee agreements [23]. As part of the patient consent form for Trusts based in England, patients will be asked to provide contact details for someone who may be willing to act as a personal consultee in the event that the patient loses capacity. Patients will also be asked to sign an advanced statement of intent, stating that should they be assessed as having lost capacity post-operatively, they would still like to be involved in the study should a consultee be available. A more detailed overview of the recruitment process is shown in Fig. 2: Recruitment overview.

**Fig. 2 Fig2:**
[figure not shown]
Recruitment Overview and Participant Flow

### Data collection (Table 1)

**Table 1 Tab1:** Sample and data collection schedule

Timepoint	Admission/Pre-Op Period	Day of Operation	Post-Op Period	
		Day 0	48 (± 4 hours) post-op	Time 1 (1 month ± 5 days)
Consent/ Agreement	X		X^a^	
AMT and/or 4AT	X		X^b^	
Collection of blood EDTA sample (6 ml)		X		
Collection of blood serum clotted sample (10 ml)		X	X^b^	
Collection of Cerebrospinal fluid (CSF) sample (≥ 2.0 ml)		X		
MMSE~ 2: SV			X^b^	
IQCODE *(To be completed by the suitable informant)*			X^c^	
Evidence of dementia from patient’s medical/GP records				X^c^
Medication information				X^c^
Collection of blood PAXgene RNA sample (2.5 ml)		X		

^a^Taken if patient’s capacity status has changed from pre-operative time period (Eng. only);

^b^Should the time window be unworkable, research nurses will collect MMSE~ 2: SV data and bloods at the next earliest opportunity but not beyond 60 h post-op;

^c^Can be gained at any point before the 1-month (± 5 days) time period elapses

#### Day of operation

The research nurse and/or anaesthetist at the time of the hip fracture operation will be responsible for collecting 18.5 ml of whole blood (1 × 6.0 ml of blood ethylenediaminetetraacetic acid (EDTA) tube, 2 × 5.0 ml serum tube and 1 × 2.5 ml PAXgene tube) and the collection of 2.0–6.0 ml of CSF (anaesthetist only).

Sites will be instructed to centrifuge CSF samples within 1 h of sample collection at 2000G for 10 min. If CSF samples are not centrifuged within a maximum of 2 h of collection, site teams will be informed to destroy the samples and alert the study management team accordingly. Blood serum samples will be centrifuged at 2000G for 15 min, within 1 h of collection. If any blood serum samples are not centrifuged within 3 h of collection, they must be rejected and destroyed; and the study management team notified accordingly. The EDTA and PAXgene samples will not require centrifugation and sites are instructed to leave these to rest at room temperature for 2 h, following inversion.

Once processed and ready for storage, the CSF, EDTA and blood serum samples will be aliquotted into 0.5 ml samples within 1.5 ml capacity Cryotubes, and stored in a specific patient Cryobox. Both the Cryobox and all of the individual Cryotubes used for patient sample storage are labelled with the patient’s unique study identifier number and colour coded to match the sample type being stored. PAXgene samples are also labelled accordingly but remain stored in their initial vacutainers, inside the corresponding patient’s Cryobox. The Cryobox will then be stored in a -80° Celsius freezer at the local research site. All of the sample collection, processing and storage times for each patient will be recorded within the study’s electronic database for monitoring purposes.

Once a site has successfully recruited and collected samples for 10 patients, the study management team will arrange for a courier to collect and deposit the samples at the Norwich Biorepository for long-term storage, until the final sample analysis is ready to be started. All sample transfers will be completed on a same day delivery basis, using dry ice to maintain sample cooling. Once at the Norwich Biorepository, samples will be monitored against the electronic database records and sample transfer log, for completeness and accuracy. Samples will then be deposited in a -80° Celsius freezer within the Norwich Biorepository. Any discrepancies will be followed up with the local research team and recorded in the electronic database accordingly.

Spinal anaesthesia will be performed according to local trust procedures. After placement of the needle to deliver the spinal anaesthetic, and prior to administration of the anaesthetic agent, a sample of between 2 and 6 ml of CSF will be collected. Patients unable to provide a sufficient CSF sample will be withdrawn from the study and any prior samples collected destroyed according to Local Trust Policy.

During collection of the CSF, the patient will be monitored. Should the patient’s discomfort become too great, the anaesthetist will stop collecting the CSF. Headaches (‘post-dural-puncture headache’ or ‘PDPH’) are a common side effect of spinal anaesthesia and typically occur within two to 3 days following the procedure. After taking advice from anaesthetists, it was identified that the risk of patients experiencing a PDPH may be slightly higher for patients taking part in this study because of the additional CSF withdrawn. The incidence of PDPH’s will therefore be monitored as part of routine care using standard local procedures. Any PDPH observed by the clinical team will be assessed for severity and reported as an adverse event. The incidence rates of PDPH’s will be monitored and review by the Data Monitoring and Ethics Committee (DMEC) and Study Steering Committee (SSC). However, the risk is expected to be negligible.

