## Methods

### Aims and objectives

In order to have specific measures informing on the severity of prevalent systemic inflammation at the time of lumbar puncture (i.e., the time of CSF collection), matched to those inflammatory mediators occurring in the CSF, we will quantify inflammatory mediators (including but not limited to IL-1β, TNF-α, IL-6) in both peripheral blood and in CSF. In order to assess brain injury we will measure CSF markers of brain injury (including but not limited to total and phosphorylated tau [T-tau and P-tau, respectively], neurofilament light [NfL] and neurogranin). Brain injury markers will also be measured in blood. Aβ42/40 ratio in CSF and plasma, measured using immunoassays (Meso Scale Discovery and Simoa methods, respectively), will be used as a biomarker of cerebral Aβ pathology. We will also collect an additional 2.5 ml of whole blood from patients. Several studies have recently been published using PAXgene blood collection tubes for later transcriptomic analysis. Our intention is to place ourselves in the position to examine blood signatures that associate with, and may be predictive of, particular CSF and clinical outcomes in our patients for later analysis. Banking these samples will enable further in-depth analysis and is in accordance with the trial ethical approval and consent process.

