#### Post-op 48 h (± 4 h)

2 × 5.0 ml blood (serum tube) will be collected from the patient. Every effort will be made to collect post-operative bloods within this time window, but this may not always be possible. Therefore, research nurses will collect the MMSE~ 2: SV data and bloods at the next earliest opportunity but not beyond 60 h post-op. The time point at which these samples and data are collected will be noted and fed into the analysis. Sites consistently collecting samples outside the 48 (± 4 h) window will be reviewed by the Study Management Group (SMG) who will decide if they should be withdrawn. For patients recruited on a Thursday or Friday, it is accepted that this follow-up may not be possible due to insufficient Research Nurses across weekends.

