#### Secondary hypothesis

The secondary hypothesis is that the magnitude of the brain inflammatory response will predict the quantity of specific brain injury markers (phospho-tau, NfL, neurogranin, synaptotagmin, SNAP-25) measured in the CSF. The strength of inter-relationship between the inflammatory and injury markers outlined will be examined using correlation coefficients. These will also be adjusted for potential confounding factors using partial correlation coefficients.

Analysis of the samples will take place at UEA, Trinity College Dublin and the University of Gothenburg. Should additional information become available during the course of the study, we will ensure that we use the most appropriate analysis available to answer the research questions.
CSF will be analysed for a number of inflammatory and neuronal injury markers. These include, but are not limited to: TNF-α, IL-1RA, IL-1β, IL-6, sTREM2, YKL-40, T-tau, P-tau, Aβ38, Aβ40, Aβ42, neurogranin, synaptotagmin and SNAP-25;Blood collected pre-operatively and at 48 h (± 4 h) will be analysed for TNF-α, IL 1RA, IL-1β, IL-6, T-tau and NfL;Blood collected pre-operatively will also be genotyped for the APOE ε2/ε3/ε4 polymorphism at UEA;PAXgene blood for later transcriptomic analysis looking for blood signatures that associate with, and may be predictive of, particular CSF and clinical outcomes in our patients.

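### Plasma Aβ42/40 is named as a biomarker, but the sample-handling and assay sections provide neither plasma nor a blood Aβ assay

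*Protocol article*

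**What the plan says.** All references are to the Protocol article.

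- **Aims and objectives** plans the ratio in two fluids, each with its own platform: "Aβ42/40 ratio in CSF and plasma, measured using immunoassays (Meso Scale Discovery and Simoa methods, respectively), will be used as a biomarker". Plasma is paired with Simoa and CSF with Meso Scale Discovery.
- **Day of operation** lists the blood drawn as one 6.0 ml EDTA tube plus "2 × 5.0 ml serum tube and 1 × 2.5 ml PAXgene tube". On processing it says "Blood serum samples will be centrifuged at 2000G for 15 min, within 1 h of collection", and for the other tubes "The EDTA and PAXgene samples will not require centrifugation and sites are instructed to leave these to rest at room temperature for 2 h". On storage, "the CSF, EDTA and blood serum samples will be aliquotted into 0.5 ml samples within 1.5 ml capacity Cryotubes", which then go into a -80 °C freezer.
- **Post-op 48 h (± 4 h)** adds only serum: "2 × 5.0 ml blood (serum tube) will be collected from the patient".
- **Secondary hypothesis** lists the blood assays as TNF-α, IL-1RA, IL-1β, IL-6, T-tau and NfL. It adds a genetic test, "Blood collected pre-operatively will also be genotyped for the APOE ε2/ε3/ε4 polymorphism at UEA", and later transcriptomics on the PAXgene tube. Aβ38, Aβ40 and Aβ42 appear in the CSF list only.

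**The concern.** One section commits to a measurement in plasma. The section that tells sites how to handle each tube rules out the step that would produce plasma, and the assay section does not list the measurement for blood.

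The conflict cannot be put down to a journal article shortening a fuller protocol. The handling text is not silent: it gives spin speeds, times and rejection limits for CSF and serum, and then expressly exempts the EDTA tube.

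At stake is one named biomarker. If plasma Aβ is truly wanted, each patient handled under the present rule is a patient without it, and the gap cannot be filled later. If it is not wanted, the article promises a measure that the study will not deliver.

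**Working it through.** No power or sample size figure is in dispute. The check traces each blood tube from collection to assay.

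**1. Is the tube list complete?** The article states a total of 18.5 ml of blood on the day of operation. From its own tube list: 6.0 + (2 × 5.0) + 2.5 = 18.5 ml. The figure is reproduced, so no further tube is hidden in the total.

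**2. Which tubes end as plasma?**

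| Draw | Tube | Number | Spun? | Stored as | Plasma? |
|---|---|---|---|---|---|
| Day 0 | EDTA | 1 | No, rested 2 h at room temperature | 0.5 ml portions, -80 °C | No |
| Day 0 | Serum | 2 | Yes, 2000G for 15 min | 0.5 ml portions of serum, -80 °C | No |
| Day 0 | PAXgene | 1 | No | Whole, in its own tube, -80 °C | No |
| 48 h | Serum | 2 | Handled as serum | Serum | No |

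Tubes yielding plasma: 0 of 1 + 2 + 1 = 4 on day 0, and 0 of 2 at 48 h.

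**3. Which tube could have given plasma?** Only the EDTA tube. The serum tubes clot and PAXgene is an RNA tube. The article does not say in words that EDTA blood is frozen whole. That is an inference from the absence of any centrifugation before it is divided and frozen.

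**4. Is the assay listed elsewhere?** Not for blood. The open-ended wording in the assay section attaches to the CSF list and not to the blood list.

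**5. Size.** Planned hip fracture patients: 200 + 200 = 400. Plasma Aβ42/40 values available under the written rule: 0 of 400.

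**6. What depends on plasma Aβ?**

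- Primary objective: CSF inflammation and injury markers; Aβ is not among them.
- Secondary objectives: Aβ positivity at baseline, with no fluid specified. CSF Aβ40 and Aβ42 are assayed, so the CSF ratio can define it.
- Secondary hypothesis: inflammation against CSF injury markers; plasma Aβ plays no part.
- Missing CSF: patients without a sufficient CSF sample are withdrawn (Day of operation), so plasma is not needed as a substitute.
- Sample size: not built on plasma Aβ.

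**The case against.** The best reply is that Aims and objectives is the outlier. The handling, 48 h and assay sections agree with one another: serum for proteins, unspun EDTA blood that suits APOE genotyping, and PAXgene for RNA. On that reading the mention of plasma is a slip or a leftover, the handling rule is as intended, and nothing is lost. This stands as an equally good explanation. It means that deleting the phrase is a full repair and not a second-best one. It does not remove the contradiction, because the article names plasma with its own assay platform, which is more than loose wording for blood.

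A second reply is that Aβ could be measured in serum. That would be a different fluid from the one named, and no serum Aβ assay is listed either.

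A reader might also infer that the Aβ-positivity objective, or a comparison of CSF with plasma, is lost. The document does not support this. It plans no CSF-plasma comparison and nowhere bases Aβ positivity on plasma.

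**Conclusion.** The point holds as a moderate internal inconsistency in a non-primary measure. Applied as written, the plan gives plasma Aβ42/40 for 0 of 400 hip fracture patients. CSF Aβ, the Aβ-positivity objective (met from CSF), the primary comparison and the sample size are unaffected, so the main conclusions are not threatened.

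It would be tempting to say that a wanted biomarker is certainly being lost in every patient. That goes too far, because the document does not settle whether plasma Aβ is still intended.

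The conclusion rests on three assumptions: sites follow the handling text as published; EDTA portions are frozen unseparated, as that text implies; and plasma cannot be recovered from blood frozen in that way. The last is general laboratory knowledge and not a statement in the article.

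**What to change.** Decide whether plasma Aβ is wanted, then bring Aims and objectives, Day of operation and Secondary hypothesis into line.

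**(a) If it is wanted.** In Day of operation, replace both parts of the EDTA instruction (no centrifugation and the 2 h rest) with a spin alongside the serum tubes. Leave the PAXgene instruction, which shares the sentence, as it is. Freeze the plasma and keep the cell fraction for APOE genotyping. Add Aβ40 and Aβ42 to the blood assay list in Secondary hypothesis. Adding a spin without removing the 2 h rest would leave Day of operation contradicting itself. The cost is a few minutes of handling per patient, since sites already spin CSF and serum. It helps only patients not yet processed.

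**(b) If it is not wanted.** Delete plasma Aβ42/40 and its Simoa platform from Aims and objectives, and state there and in Secondary objectives that Aβ status is defined by CSF. This is a change of wording only. It agrees with the handling and assay sections as they stand, and it is open at any stage of recruitment.

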#### Post-op 48 h (± 4 h)

2 × 5.0 ml blood (serum tube) will be collected from the patient. Every effort will be made to collect post-operative bloods within this time window, but this may not always be possible. Therefore, research nurses will collect the MMSE~ 2: SV data and bloods at the next earliest opportunity but not beyond 60 h post-op. The time point at which these samples and data are collected will be noted and fed into the analysis. Sites consistently collecting samples outside the 48 (± 4 h) window will be reviewed by the Study Management Group (SMG) who will decide if they should be withdrawn. For patients recruited on a Thursday or Friday, it is accepted that this follow-up may not be possible due to insufficient Research Nurses across weekends.

#### Post-op 1-month (± 5 days)

The 1-month post-op period will provide clinical teams with an opportunity to contact the patient’s General Practitioner (GP) and review their case notes to assess if the patient has a pre-existing documented diagnosis of dementia, as well as record some additional clinical measures and test results. If the patient has an eligible suitable informant, clinical teams will also use this time to complete IQCODE assessment if they have not already done so.

### Sample size

We will recruit 200 patients with dementia and hip fracture; and 200 patients without dementia but who have experienced a hip fracture. This sample size is pragmatically based upon what would appear to be achievable in the time available and with consideration of likely statistical power. Without adjustment, a sample size of 200 subjects per group will provide statistical power of 90% to detect a mean between group mean differences of 0.33 standard deviations in any outcome variable using a two-sided significance level of 5%. Assuming confounding variables entered into a General Linear Model ‘explain’ no more than 25% of the total variation (i.e. the co-efficient of determination, R2, is less than 0.25), then this sample size should provide 90%. Power to detect an ‘adjusted’ mean difference of around 0.37 residual standard deviations [27]. In either case, this would be deemed a relatively small effect to be detected with high probability.

Data will be collected initially from two different groups:
Group 1: Pre-operative acute hip fracture patients with confusion;Group 2: Pre-operative acute hip fracture patients without confusion.

In respect of Group 1 (those with confusion), the AMT (England) and 4AT (Scotland) score indicate that a patient may be living with dementia. However, this may not be confirmed until 1-month post-op when reviewing the patient’s case notes, contacting their GP or reviewing their relevant Suitable Informant’s IQCODE Scores. Based on prior research, we anticipate that up to 50% of patients who have an AMT score of 8 or less (England) or 4AT score of 1 or above (Scotland) will have dementia (diagnosed or undiagnosed/vectored) [22]. Therefore, up to 400 may need to be recruited to this group. Recruitment will be monitored and stopped for Group 1 as soon as we receive 200 patients with confirmed dementia required for the study.

We will also collect data from patients without confusion (Group 2), who are unlikely to be confirmed with dementia at 1-month post-op. These patients will be included in the non-dementia group. Again, recruitment will be monitored and stopped from this group once 200 non-dementia patients have been included. The number required from this group will be dependent upon the non-dementia confirmation rate for this group.

There will be a number of patients from Group 1 (Pre-operative acute hip fracture patients with confusion) for whom we cannot find evidence of dementia at 1-month post-op. The samples and data from this (confused, non-dementia) group will be deposited into a biobank at the Norwich Biorepository, for use in future research studies. In cases where patients were initially in Group 2 (Pre-operative acute hip fracture patients without confusion) but where evidence of dementia is available at 1 month post-op, we will reallocate these patients to the dementia patient group.

Comparable data will also be provided from a third group (Oslo Cohort) of 200 ‘stable’ patients living with a confirmed dementia diagnosis, taken from existing memory clinic data (Norwegian Registry of Persons with Cognitive Symptoms (NorCog) (Reference: S-08143a and 2017/371). Samples for this group are already available, as lumbar puncture is part of the diagnostic workup of patients included in the Norcog registry (Reference: S-08143a). These samples were analysed in 2017 at Sahlgrenska for the following: Aβ38, Aβ40, Aβ42, 10xAb42/Ab40, YKL-40, IL-1β, IL-6, IL-8, TNF-α, G36-NG2. The respective regional committee responsible have already provided permission to compare these results with those gathered in the present study.

Thus, we shall assemble data from 3 groups (hip fracture and dementia, hip fracture and non-dementia, stable and dementia), each with an expected 200 subjects. Please (see Fig. 1: Study diagram and group allocation of patients).

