#### Primary hypothesis

We will address the primary hypothesis, that systemic inflammation arising from hip fracture leads to an acute brain injury, by comparing the level of inflammatory and neuronal injury CSF and blood markers between the three groups defined above. Accordingly, we predict raised inflammatory and injury markers for the confirmed dementia-hip fracture group compared to the medically stable dementia group (Oslo cohort) and compared to the non-dementia hip fracture group.

Each of the markers will be compared across groups using a general linear model with the marker as the dependent variable (i.e. a separate model for each biomarker). The initial model will simply include group as an explanatory factor. A further model will then be constructed, including potential confounding variables, such as age, to provide an adjusted between group mean difference (comparing fracture patients with dementia to fracture patients without and fracture patients with dementia to stable dementia patients), together with 95% confidence intervals and significance test. In the event of the residuals for these models not appearing normally distributed, an appropriate transformation will be applied, such as a logarithmic transformation. We also predict that patients with dementia will have significantly worse cognitive and functional informant-based scores. A similar analysis will be conducted with cognitive and functional scores as the dependent variable.

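### The Sample size section states its 90% power too broadly (48-hour outcomes have no allowance for missed visits) and gives the adjusted 0.37 SD figure with the wrong definition of R2

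*Protocol article*

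**What the plan says.** The Sample size section of the protocol article makes two power statements.

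- Unadjusted: "Without adjustment, a sample size of 200 subjects per group will provide statistical power of 90" per cent for a difference of "0.33 standard deviations in any outcome variable using a two-sided significance level of 5" per cent.
- Adjusted: if the confounders entered in a general linear model explain "no more than 25% of the total variation (i.e. the co-efficient of determination, R2, is less than 0.25"), the same numbers should give 90% power for a "mean difference of around 0.37 residual standard deviations".

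The Primary hypothesis section shows what that model is: "Each of the markers will be compared across groups using a general linear model with the marker as the dependent variable". Its confounders are given only by example, with age named. It covers blood as well as CSF markers, and says cognitive and functional scores will be analysed in a similar way.

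The section on the 48-hour visit says: "For patients recruited on a Thursday or Friday, it is accepted that this follow-up may not be possible". The section on approaching patients post-operatively makes the same concession and encourages Monday-to-Friday recruitment. Post-operative blood and the MMSE-2:SV are collected at this visit, with an outer limit of 60 hours. The Sample size section does not mention this loss; the three groups are "each with an expected 200 subjects".

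**The concern.** The adjusted statement mixes up two different R2 values. How much of the marker's variation the confounders explain determines the size of the residual SD. How much of group membership they explain determines how far adjustment inflates the variance of the group difference. Only the second raises the detectable effect when that effect is expressed in residual SDs. The text describes the first and prints a figure that belongs to the second. The plan therefore sets no limit on the quantity that matters, and that quantity is least certain for the Oslo memory-clinic cohort, which was assembled in another setting.

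The unadjusted statement is made for every outcome, but the 200 per group behind it is not assured for outcomes measured at 48 hours. A null result for post-operative blood markers or MMSE, or for the adjusted Oslo comparison, could later be read as coming from an analysis with 90% power when its power was lower.

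**Working it through.** **Inputs.** From the Sample size section: 200 per group, two-sided 5%, 90% power, 0.33 SD unadjusted, R2 = 0.25, 0.37 residual SD adjusted. The 48-hour loss rates and the age gaps are assumptions, because the document gives neither.

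**1. The plan's unadjusted figure.** Power = Φ(δ/√(2/n) − 1.960). With n = 200, √(2/200) = 0.100, so power at 0.33 SD is Φ(3.30 − 1.96) = Φ(1.34) = 91%. The effect with 90% power is (1.960 + 1.282) × 0.100 = 0.324 SD, or 0.325 with the t distribution. The plan's 0.33 is this value rounded up.

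**2. The plan's adjusted figure.** In residual SDs, the detectable effect is 0.325/√(1 − R2g), where R2g is the R2 from regressing group on the confounders. With R2g = 0.25, this is 0.325/0.866 = 0.375 (0.374 from 0.324), which is the plan's figure of about 0.37. Power at exactly 0.37 is then Φ(3.70 × 0.866 − 1.96) = Φ(1.24) = 89%, again a matter of rounding.

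**3. The same figure on the R2 that the text defines.** If the confounders explain 25% of the marker's variation and are unrelated to group, there is no variance inflation. The effect with 90% power stays at about 0.325 residual SD, or 0.325 × 0.866 = 0.28 total SD. Power at 0.37 residual SD is Φ(3.70 − 1.96) = Φ(1.74) = 96%.

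**4. What an unbounded R2g could do.** Take one confounder, such as age, whose means differ by g within-group SDs between two equal groups. Then R2g = g²/(g² + 4).

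| Assumed gap g (SD) | R2g | Effect with 90% power (residual SD) | Power at 0.37 |
|---|---|---|---|
| 1.15 | 0.25 | 0.37 | 89% |
| 1.5 | 0.36 | 0.325/0.800 = 0.41 | Φ(3.70 × 0.800 − 1.96) = 84% |
| 2.0 | 0.50 | 0.325/0.707 = 0.46 | Φ(3.70 × 0.707 − 1.96) = 74% |

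**5. Outcomes at 48 hours.** If recruitment is even over five weekdays, Thursday and Friday recruits are 2/5 = 40%. Missing every one of these visits leaves 120 per group; missing half of them (20%) leaves 160. Loss is taken as equal in the two fracture groups.

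| Assumed loss | n per group | Power at 0.33 SD | Effect with 90% power |
|---|---|---|---|
| 0% | 200 | 91% | 0.32 SD |
| 20% | 160 | Φ(0.33/0.1118 − 1.96) = 84% | 3.242 × 0.1118 = 0.36 SD |
| 40% | 120 | Φ(0.33/0.1291 − 1.96) = 72% | 3.242 × 0.1291 = 0.42 SD |

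**The case against.** The best defence is that the main figure is sound. It reproduces, and it describes the pre-operative CSF markers of the primary objective, which the 48-hour visit does not touch. The plan puts CSF collection first and is open about the weekend gap. On the literal R2, the adjusted statement errs on the cautious side. The source cited for 0.37 cannot be seen and may define R2 correctly. The figure could also come from re-expressing 0.324 total SD in residual units, since 0.324/0.866 = 0.374; but the adjusted power there is 96%, so the 90% attached to it would still be wrong. All of this limits the size of the point without removing it: the printed definition and the printed figure do not belong together, and the power claim is still made for all outcomes.

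Three stronger readings are tempting, and the document does not support them.

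- *That 90% power is missing for the primary markers because nine CSF markers are each tested against two comparators.* Multiple testing at 5% raises the chance of a false positive; it does not lower the power of each test. A primary marker, a multiplicity correction or a rule requiring both comparisons may stand in the statistical analysis plan, which the article refers to and which is not shown.
- *That all Thursday and Friday recruits lose the 48-hour visit.* The text says only that the visit might not be feasible. The window runs from the operation, so an operation at 21:00 on Friday reaches its 60-hour limit at 09:00 on Monday. The 40% is an upper bound under even recruitment, not a forecast.
- *That the adjusted Oslo comparison is known to be underpowered.* No ages are given for either cohort, so the gaps in the table are illustrations.

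**Conclusion.** The point holds as a correction to two power statements, not as a failure of the sample size. The 90% at 0.33 SD (computed 91%) is correct for a single unadjusted comparison of a pre-operative marker with 200 per group.

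The adjusted figure is wrongly described. As defined in the text, 90% power is at about 0.325 residual SD and 0.37 has 96%. As calculated, 0.37 holds only while the confounders explain no more than a quarter of group membership, a limit that the plan does not state.

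The claim for every outcome does not extend to 48-hour blood markers and MMSE. There, power at 0.33 SD is 84% with 20% loss and 72% with 40% loss, both rates assumed and loss taken as equal between groups. That the plan foresees some loss and allows for none rests on the text alone.

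**What to change.** Change the Sample size section as follows.

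1. Limit the 90% statement to one unadjusted comparison of a marker measured on pre-operative samples with 200 per group.
2. Define R2 as that of group membership regressed on the confounders. Give the effect with 90% power over a range, and separately for the Oslo comparison: for example 0.37 residual SD at R2 0.25, 0.41 at 0.36 and 0.46 at 0.50. Label these R2 values as assumptions unless the two cohorts' ages are used to set them.
3. For post-operative blood and MMSE, state the assumed loss and the resulting power: for example 84% at 0.33 SD with 160 per group (0.36 SD detectable at 90%), and 72% with 120 per group (0.42 SD), the latter marked as an upper bound on loss.

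This is wording only, with no new data and no change to recruitment. The cost is a less favourable stated power for the 48-hour outcomes and possibly for the adjusted Oslo comparison.
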